**Methods/design:**

A multicenter randomized controlled trial will be performed in seven hospitals. Six hundred participants will be stratified into two strata (IBS-C or IBS-D). Then, patients within each stratum will be divided into an experimental group and a control group randomly. The experimental group is treated with acupuncture while the control group is treated with Western medicine. All the patients will receive a 6-week treatment and a 3-month follow-up. The primary outcome is the IBS-Symptom Severity Score (IBS-SSS), the secondary outcome is the score of the IBS-Quality of Life (IBS-QoL).The correlation between IBS-gene subtypes and acupuncture effect will be detected based on polymerase chain reaction-restriction fragment length polymorphism (PCR-RFLP). Outcome measures (including primary and secondary outcome measures) are collected at baseline,1 week, 2 weeks, 4 weeks, and 6 weeks of the intervention, and 12 weeks after the intervention.

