### Study design

This study is a multicenter, stratified randomized controlled trial (RCT), comparing acupuncture to standard pharmacological treatment for two subtypes of IBS: IBS-C (constipation-predominant IBS) and IBS-D (diarrhea-predominant IBS). The study is being conducted in the following seven hospitals: Jiangsu Hospital of TCM, Wuxi Hospital of TCM, Nantong Hospital of TCM, Nanjing Hospital of Chinese Medicine, Zhenjiang Riverside Hospital, Kunshan Hospital of TCM, and Shuyang Hospital of TCM. The study will be carried out according to the principles of the Declaration of Helsinki (version Edinburgh 2000).

This study will be performed over a period of 19 weeks: 1 week of wash-out, 6 weeks of treatment, and 12 weeks of post-treatment follow-up. All eligible patients will be stratified into two strata: IBS-C or IBS-D. The patients within each stratum will then randomly divided to either an acupuncture group or a control group receiving standard pharmacological treatment. Outcomes will be assessed at baseline, during the treatment and at the end of the follow-up. Figures 1 and 2 illustrate the time schedule of enrollment, interventions, assessments, and participant visits.

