### Randomization and blinding

The Good Clinical Practice (GCP) Center of Jiangsu Province Hospital of TCM will be responsible for generating the randomization sequence. All eligible participants will be told not to take any treatment for IBS for 1 week (the wash-out period). After the wash-out period, all the participants will be stratified into IBS-C or IBS-D subgroups and then randomly allocated to either the acupuncture group or the control group by a central randomization system. An allocation ratio of 2:1 will be used in the acupuncture to control group assignment. Only the outcome assessors and the statisticians will be blinded to the allocation. The outcome assessors and the statisticians will not participant in the treatment, they will perform the outcome evaluation and the statistical analysis independently.

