**Fig. 3 Fig3:**
[figure not shown]
Locations of acupoints: acupuncture group

The patients in the control group will receive standard pharmacological treatment based on the IBS subtype. Patients with IBS-C will take macrogol 4000 powders (Fu Song, two bags per day, dissolved in a glass of water before taking) for 6 weeks. Patients with IBS-D will take pinaverium bromide tablets (Dicetel, 50 mg tid, swallowing pills with water during meals without breaking, chewing or dissolving) for 6 weeks.

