Statistical analysis of all data in this study will be performed by a specialized statistician, who is blinded to the treatment allocation. Statistical Package for the Social Sciences (SPSS) V.24.0 (SPSS Inc., Chicago, IL, USA) will be used for data analysis. All analysis will be on the basis of the intention-to-treat (ITT) population and the per-protocol (PP) population. ITT requires all participants in a clinical trial to be included in the analysis in the groups to which they were randomized, regardless of any departures from randomized treatment. The PP population is usually defined as all patients completing the study without major protocol deviations – that is those who followed the rules of the study. The results of each population will be compared for stabilization. Last-observation-carried-forward will be used in the case of missing data. The principal investigator will take responsibility for the results of the data analysis. In terms of data description, quantitative and qualitative data will be presented as mean ± standard deviation, frequency, percentages or constituent ratios, respectively. Other covariates such as age, gender, ethnicity, disease duration, marital status, educational level, weight (in kilograms), and height (in meters) will be considered for further revision. In case of normality of distribution and homoscedasticity, the baseline characteristics will be performed using the analysis of covariance (ANCOVA) model, and the multiple comparisons will be performed with the Least Significant Difference test. In addition, a repeated- measure analysis of variance (rm-ANOVA) will be used to determine, within each group, the difference between baseline and 1, 2, 4, 6, and 18 weeks for both the IBS-SSS and the IBS-QoL. On this occasion of non-normal distribution data and heteroscedasticity data, the non-parametric Kruskal-Wallis test will be performed, and the Nemenyi test will be done to identify the difference between the groups. Pearson’s chi-squared test will be used in the transformed categorical data. Lastly, we will conduct rm-ANOVA to analyze genotype-related effects on treatment response. The Huynh-Feldt correction will be used if the assumption of sphericity is violated. A two-sided *p* value of less than 0.05 will be considered statistically significant for all analyses.

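### Subtype stratifies the randomisation and decides the comparator drug, but the published analysis text never uses it, so a pooled difference may hide two different drug comparisons

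*Protocol article*

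**What the plan says.** All places are in the protocol article.

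- **Randomization and blinding:** "all the participants will be stratified into IBS-C or IBS-D subgroups and then randomly allocated" to acupuncture or control, in a 2:1 ratio. Study design says the same: "The patients within each stratum will then randomly divided to either an acupuncture group or a control group". Subtype is the only stratification factor named.
- **Acupuncture and the control group:** "The patients in the control group will receive standard pharmacological treatment based on the IBS subtype". In detail, "Patients with IBS-C will take macrogol 4000 powders" and "Patients with IBS-D will take pinaverium bromide tablets". Acupuncture is the same in both subtypes.
- **Sample size calculation and statistical analysis, sample size part:** one expected improvement per arm (115 and 105 IBS-SSS points), one SD (37), and 322 + 161 participants, raised to 400 + 200 for 20% drop-out. No subtype split is given.
- **Same section, analysis part:** covariates are introduced with "Other covariates such as age, gender, ethnicity, disease duration, marital status, educational level", followed by weight and height. The text then names ANCOVA, Least Significant Difference comparisons, repeated-measures ANOVA within each group, Kruskal-Wallis with Nemenyi, chi-squared, and a repeated-measures ANOVA for genotype. Subtype does not appear as a covariate, factor, stratum, interaction or subgroup.

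**The concern.** Subtype does two jobs in this design. It is the stratification factor, and it fixes which drug a control patient takes. The control arm is therefore two drugs in two patient groups, and the trial is two active-control comparisons run side by side. Such a factor would be expected to enter the between-arm analysis and the reporting.

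Two things are at stake. The first is interpretation: a benefit over one drug and none over the other could be reported as a benefit over standard drug treatment in general, at a size set partly by how many patients of each subtype were recruited. The second is efficiency: if subtype predicts change in IBS-SSS, leaving it out of the model leaves its variation in the error term, although randomisation has already balanced it between arms.

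**Working it through.** **Inputs from the sample size text.** Difference 115 − 105 = 10 points; SD 37; ratio 2:1; 5% type I error (two-sided, from the analysis part); 80% power; 20% drop-out; 400 + 200 randomised.

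**Assumption.** The split between IBS-C and IBS-D is not given. A stratum share of 20% to 80% is used, with 50:50 as the reference.

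**1. The plan's own figure.** For a 2:1 design,

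n(control) = 1.5 × [37 × (1.960 + 0.842) / 10]² = 161.2.

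Rounded up this is 162 control and 324 acupuncture; the plan has 161 and 322, where power is 79.96% (normal approximation). A one-sided test would give 127 and 254, which does not match. The stated size is thus a sound two-sided calculation for one contrast of all acupuncture patients against all controls.

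**2. What a pooled difference estimates.** With IBS-C share p, pooled effect = p × (effect vs macrogol) + (1 − p) × (effect vs pinaverium). For illustrative true effects of 20 and 0 points:

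| IBS-C : IBS-D | Pooled effect |
|---|---|
| 30:70 | 0.3 × 20 = 6 |
| 50:50 | 0.5 × 20 = 10 |
| 70:30 | 0.7 × 20 = 14 |

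With effects of 10 and 10, the pooled effect is 10 at any mix, and pooling misleads nobody.

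**3. Precision within a subtype.** After 20% drop-out, 320 + 160 patients remain. A half-share stratum has 160 + 80, so SE = 37 × √(1/160 + 1/80) = 5.07. Power for 10 points (two-sided t-test):

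| Stratum share | Acupuncture / control | Power |
|---|---|---|
| 20% | 64 / 32 | 23.5% |
| 30% | 96 / 48 | 33.0% |
| 40% | 128 / 64 | 41.9% |
| 50% | 160 / 80 | 50.2% |
| 60% | 192 / 96 | 57.7% |
| 70% | 224 / 112 | 64.4% |
| 80% | 256 / 128 | 70.2% |

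**4. Interaction.** At 50:50, SE = √2 × 5.07 = 7.17. The difference between subtype effects detectable with 80% power is 2.8 × 7.17 = about 20 points. At 20:80 the SE is 37 × √(1.5/32 + 1.5/128) = 8.96, and about 25 points is detectable.

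**5. Cost of omitting subtype.** Take 322 + 161 patients, a 50:50 split, SD 37 within each subtype, and subtype means differing by B SDs. The SE used is too large by √(1 + 0.25B²).

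- B = 0.5: factor 1.031; actual type I error 0.043; power 78.2%.
- B = 1: factor 1.118; actual type I error 0.028; power 72.9%.

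The error is on the conservative side, and small unless the subtypes differ markedly.

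**The case against.** The strongest reply is that silence is not exclusion. This is a journal article, and the full protocol and analysis plan are not shown. The covariate list is introduced as other covariates, by way of example, so it does not fix a model without subtype. A reader might infer that the plan excludes subtype; the text shows only that subtype is not mentioned. The Least Significant Difference, Kruskal-Wallis and Nemenyi procedures suit more than two groups and could have been meant for four subtype-by-arm cells, although the article never says so and its sample size speaks of one acupuncture and one control group.

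Four further inferences are tempting, and the document does not support them:

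- **That a pooled result can describe neither comparison.** Acupuncture against the standard drug for the patient's subtype is a legitimate strategy comparison, and its average has a meaning. It misdescribes its components only if effects differ by subtype, and the article offers no data that they do.
- **That leaving out centre is the same fault.** The trial runs at seven hospitals, but centre is not a stated stratification factor, so nothing in the design is contradicted.
- **That baseline IBS-SSS is ignored.** It enters the repeated-measures ANOVA as a time point. Using it as a covariate is an improvement, not a correction of an omission.
- **That the trial fails on power.** The article claims no power within subtypes, and the pooled calculation reproduces. If the SD of 37 already includes between-subtype spread, the planned pooled power is not reduced either.

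What stands is narrower. The section goes as far as naming height and marital status as covariates, yet gives no role to the one factor that both structures the randomisation and selects the comparator.

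**Conclusion.** The concern holds as a gap between design and analysis, not as an arithmetical error. Subtype is the stratification factor and sets the comparator; the trial is sized for one pooled contrast; and the published analysis text gives subtype no role.

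The harm to interpretation is conditional. It arises only if effects differ between IBS-C and IBS-D, but without subtype-specific estimates readers could not tell whether they do. The 20-and-0 example was chosen to average to the planned 10 and is not a forecast. The loss of efficiency is modest and conservative: 78.2% power if subtype means differ by half an SD, on the assumptions shown.

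The subtype power figures (about 50% at an even split, about 24% to 70% over shares of 20% to 80%) rest on an assumed split, the same 10-point effect and SD in both subtypes, and 20% of patients lost to the analysis. They show how cautiously subtype results must be read. The change is worth making, but the pooled comparison is not invalid without it.

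**What to change.** In the between-arm analysis of IBS-SSS:

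1. Include subtype as a factor and baseline IBS-SSS as a covariate.
2. Report the treatment-by-subtype interaction, and the acupuncture-minus-drug difference with its 95% CI separately for IBS-C (against macrogol) and IBS-D (against pinaverium), whatever the interaction test shows.
3. Word conclusions against the named comparator.
4. State that the 80% power applies only to the pooled contrast, and that a non-significant subtype result or interaction is not evidence of equal effects.

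Adjustment for centre is optional.

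The cost is a few model terms and one table. Subtype is known at randomisation and baseline IBS-SSS is already collected, so no new data or patients are needed. The downside is wider intervals for the subtype estimates. The article reports 540 participants recruited and the trial still ongoing, so the change should be fixed and dated before allocation is unblinded for analysis. If the full analysis plan already contains these terms, citing it is enough.

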### Sample size calculation and statistical analysis

Based on our previous clinical experience and the previous literature, we anticipate an improvement of 115 points in the acupuncture group and 105 points in the control group on the IBS-SSS. The standard deviation is set at 37, and the ratio between the acupuncture and control groups is 2:1. The sample size is calculated with 80% power and 5% type I error using G*Power software (version, Franz Faul, Universitat Kiel, Germany). This resulted in a required sample size of 322 participants in the acupuncture group and 161 participants in the control group. After accounting for a 20% drop-out rate, 400 participants in the acupuncture group and 200 participants in the control will be included.

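### When parametric assumptions hold, the plan states no acupuncture-versus-drug test of IBS-SSS: the test tied to the primary outcome is a within-arm comparison with baseline

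*Protocol article*

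**What the plan says.** All references are to the Protocol article.

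- **Aim** (Study design): the trial is described as "comparing acupuncture to standard pharmacological treatment for two subtypes of IBS". Outcome assessment names IBS-SSS as the primary outcome, measured at baseline and at 1, 2, 4, 6 and 18 weeks.
- **Sample size** (Sample size calculation and statistical analysis): the expected effect reads "we anticipate an improvement of 115 points in the acupuncture group and 105 points in the control group on the IBS-SSS", which is a gap of 10 points. For the spread the text has "The standard deviation is set at 37". For allocation it has "the ratio between the acupuncture and control groups is 2:1". For error rates it has "The sample size is calculated with 80% power and 5% type I error". The result is 322 and 161 evaluable patients, and 400 and 200 enrolled.
- **Parametric branch** (same section): if data are normal and homoscedastic, "the baseline characteristics will be performed using the analysis of covariance (ANCOVA) model", with Least Significant Difference tests for multiple comparisons. In addition, for IBS-SSS and IBS-QoL alike, a repeated-measures ANOVA "will be used to determine, within each group, the difference between baseline and 1, 2, 4, 6, and 18 weeks".
- **Non-parametric branch** (same section): otherwise "the non-parametric Kruskal-Wallis test will be performed, and the Nemenyi test will be done to identify the difference between the groups".
- **Remaining tests** (same section): a chi-squared test for categorised data and a repeated-measures ANOVA for genotype effects.

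**The concern.** The question is whether acupuncture does better than drug treatment. A test of each arm against its own baseline does not answer it. Improvement from baseline mixes treatment effect with natural fluctuation, regression to the mean (entry requires a minimum IBS-SSS) and expectation. The plan itself expects more than 100 points of improvement in both arms.

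ANCOVA would be the natural between-arm tool. As written, it is pointed at baseline characteristics, where any difference in a randomised trial is due to chance. The parametric branch states no group effect, group-by-time term or arm contrast for IBS-SSS.

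At stake is the primary conclusion. Followed literally, the parametric branch yields two within-arm p-values and no estimate of the treatment difference for which the trial was sized. Whether a between-arm test is run at all would then depend on a distribution check made after the data are in.

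**Working it through.** **Step 1. What the sample size presupposes.** Inputs from the sample size paragraph: difference 115 − 105 = 10 points, SD 37, ratio 2:1, power 80%, alpha 5%. The statistical paragraph makes tests two-sided.

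Control n = (1 + 1/2) × [37 × (1.960 + 0.842) / 10]² = 161.2, rounded up to 162, with 324 for acupuncture. The plan states 161 and 322, so its figure is reproduced to within rounding. Power at 322 and 161 is 80.0% by the normal approximation and 79.8% by the noncentral t. A one-sided version gives 127 controls and does not reproduce the plan. The number therefore belongs to a two-sided, two-sample comparison of improvement between arms.

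**Step 2. Which stated tests make that comparison.**

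| Stated test | Applied to | Condition | Compares arms on IBS-SSS? |
|---|---|---|---|
| ANCOVA with LSD | baseline characteristics | parametric | no, as written |
| rm-ANOVA | IBS-SSS and IBS-QoL, against baseline | no condition of its own; follows the parametric sentence | no, within each group |
| Kruskal-Wallis and Nemenyi | outcome not named | non-normal or heteroscedastic | yes, if applied to IBS-SSS |
| Chi-squared | categorised data, not specified | none given | not stated |
| rm-ANOVA | genotype effects on response | none given | no |

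The parametric branch contains no stated test that matches Step 1.

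**Step 3. What the within-arm test would show with no treatment difference.** Suppose both arms truly improve by 105 points. The plan does not say whether 37 is the SD of change, so both readings are shown.

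Within-arm t = 105 / (SD of change / √n)

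- SD of change 37: 105 / (37/√161) = 36.0 and 105 / (37/√322) = 50.9.
- 37 as a single-visit SD with zero correlation between visits (an assumption), so SD of change = 37 × √2 = 52.3: t = 25.5 and 36.0.

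Either way both arms are far beyond any significance threshold, although the true difference is zero.

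**Step 4. The between-arm test for contrast.** With SD of change 37, the standard error of the difference is 37 × √(1/322 + 1/161) = 3.57 points. A true difference of 10 points gives an expected statistic of 10 / 3.57 = 2.80, and a true difference of zero gives 0. Only this comparison separates the two situations.

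**The case against.** **The ANCOVA sentence is garbled, and an adjusted comparison may have been meant.** This is a fair point. The sentence before it lists covariates such as age, gender and disease duration, and the within-group analysis is introduced as an addition to the ANCOVA. A baseline-adjusted comparison of arms is a plausible intention, so a reader should not infer that the investigators plan no parametric between-arm test. What stands is that the text does not say so, and a prespecified primary analysis should not have to be guessed.

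**A between-group test does exist.** It does, in the non-parametric branch, so it would be wrong to say that the plan has no between-group test at all. That test is also sound: with two arms Kruskal-Wallis reduces to the Wilcoxon-Mann-Whitney test. A reader might infer that it ignores the baseline score, but the plan does not say whether raw or change scores are ranked. Its limits are that it is conditional and gives no difference in points. How often the distribution check would lead to it cannot be judged, because the documents give no figures on the shape of the data.

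**Nothing says superiority will be claimed from within-arm p-values.** That is correct, and such a claim should not be attributed to the authors. The gap is that the written parametric analysis gives them nothing else to base the comparison on.

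**Detail may be left to a separate analysis plan.** This would answer an omission. Here the article states a test for the primary outcome, and that test does not match the article's own aim and sample size. The Trial status section also gives non-specific statistical methods as one reason for the revision that produced this text.

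**Conclusion.** The point holds for the parametric branch. There the analysis section states no acupuncture-versus-drug test of IBS-SSS, while the aim and the sample size both require one. The within-arm test that is stated would be significant in both arms whether or not the arms differ: t is about 36 and 51 with 105 points of improvement in each arm and 37 taken as the SD of change, and about 25 and 36 with the larger SD of 52.3. The conclusion does not depend on which reading of the SD is correct.

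The defect is one of wording in the analysis section. It does not show that the sample size is wrong; that figure reproduces. Confidence is high on what the text says and lower on what was intended. It should be settled before analysis, because it concerns the primary comparison.

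**What to change.** Rewrite the ANCOVA sentence so that it defines the primary analysis:

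- One between-arm model of IBS-SSS at a single named primary time point, for example week 6, the end of treatment. There are five post-baseline visits, so without a named visit the primary contrast stays undefined.
- Either ANCOVA, or a repeated-measures model with the treatment contrast at that visit. Include treatment, baseline IBS-SSS and IBS subtype (the randomisation stratum).
- Report the adjusted mean difference in points with its 95% CI, and use the same model for IBS-QoL.
- Keep this model primary whatever the distribution check shows, with the rank test as a sensitivity analysis.
- Make the within-group rm-ANOVA descriptive, and drop significance tests of baseline characteristics.

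The cost is wording only. The sample size is unchanged, no new data are needed, and SPSS, the stated software, fits these models. The article describes the trial as still ongoing with 540 recruited, so at that stage the change could precede the analysis.

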### Outcome assessment

The primary outcome measure of this trial is the IBS-Symptom Severity Score (IBS-SSS), a validated scoring system for assessing the severity of IBS [24, 25]. The questionnaire is scored from 0 to 500 and is composed of five 100-point scales that measure the severity of pain, duration of pain, severity of abdominal distention, dissatisfaction with bowel habits, and disruption in life quality. The scores are classified into no IBS (< 75), mild IBS case (75–175), moderate IBS case (175–300), and severe IBS case (> 300) [25]. IBS-SSS is assessed at baseline, 1, 2, 4, 6, and 18 weeks.

The secondary outcome measures include the IBS-Quality of Life (IBS-QoL) and genotyping of the patients’ serotonin-related genes. The IBS-QoL is a 34-item questionnaire for determining the degree to which IBS interferes with the patient’s quality of life [26]. It is composed of eight dimensions, including dysphoria, interference with activity, body image, health worry, food avoidance, social reaction, sex, and relationships. Each item is evaluated on a 5-point rank scale with a higher score indicating a better quality of life. The IBS-QoL will be measured at baseline and 6 and 18 weeks.

DNA isolation and genotyping will be performed to study the possible correlation between the therapeutic effectiveness of acupuncture and the following polymorphisms of serotonin-related genes: (1) *HTTLPR* (*L/L*, *L/S*, *S/S*), (2) *STin2 VNTR* (*STin2 12/12*, *STin2 12/10*, *STin2 12/9*, *STin2 10/10*, *STin2 9/9*), and (3) *rs25531* (*rs25531-G*). The patients’ blood samples will be collected at the baseline. The correlation between IBS-gene subtypes and acupuncture effect will be detected based on cleaved amplification polymorphism sequence-tagged sites.

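### If the chi-squared test for transformed categorical data is meant for the four IBS-SSS severity bands, it ignores both their order and the baseline score and has low power for the planned effect

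*Protocol article*

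**What the plan says.** The section on sample size and statistical analysis lists tests by type of data. For categorical data it says only that Pearson's "chi-squared test will be used in the transformed categorical data". It gives no variable, cut points, time point or role for that analysis, and names no ordinal or baseline-adjusted method for categorical data. It also states: "A two-sided *p* value of less than 0.05 will be considered statistically significant for all analyses".

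The section on outcome assessment makes the IBS-SSS, scored 0 to 500, the primary outcome. In describing the scale it gives four ordered classes with cuts at 75, 175 and 300. The middle two read "mild IBS case (75–175), moderate IBS case (175–300", so a score of exactly 175 falls in both. That section does not say that band membership is an outcome to be tested.

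The trial is sized on the continuous score: "we anticipate an improvement of 115 points in the acupuncture group and 105 points in the control group on the IBS-SSS". The next sentence adds: "The standard deviation is set at 37, and the ratio between the acupuncture and control groups is 2:1".

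**The concern.** The word transformed suggests a quantitative variable cut into classes, and the IBS-SSS bands are the only such cut of an outcome in the document. On a two-arm by four-band table, Pearson's test has 3 degrees of freedom. It treats the bands as unordered labels, so it responds to any difference in pattern, including one in which neither arm is better. It yields no effect estimate. It also ignores the score at entry, which largely determines the band at the end.

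At stake is how a severity-grade result would be read. Since the 0.05 threshold applies to every analysis, this test would receive a significance verdict. If acupuncture delivered exactly the planned advantage, the banded result would still probably be non-significant, and could be taken to contradict a positive result on the continuous score.

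**Working it through.** **Inputs from the protocol.** Difference 115 − 105 = 10 points; SD 37; allocation 2:1; for power, "The sample size is calculated with 80% power and 5% type I error", with two-sided testing. The evaluable sample is given as a "required sample size of 322 participants in the acupuncture group and 161 participants in the control group". The enrolment target follows: "After accounting for a 20% drop-out rate, 400 participants in the acupuncture group and 200 participants in the control will be included". Entry requires a baseline IBS-SSS of at least 75. Band cuts are 75, 175 and 300.

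**Assumptions (not in the protocol).** Baseline IBS-SSS is normal with mean 200–300 and SD 50–90 before truncation to 75–500. The correlation r between baseline and improvement is 0, 0.4 or 0.7. Where 600 patients are analysed, the full 10-point effect is taken to apply to all of them.

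**Step 1: the plan's own figure.** Control-group size = (1.960 + 0.842)² × 37² × (1 + 1/2) / 10² = 7.849 × 1369 × 1.5 / 100 = 161.2. Rounded up, this is 162 control and 324 acupuncture, against the stated 161 and 322. The stated numbers give 79.96% power (normal approximation) or 79.8% (noncentral t). Dividing by 0.8 gives 202 and 403, against the stated 200 and 400. The figure reproduces.

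**Step 2: why the baseline matters.** With 322 + 161 patients, √(322 × 161 / 483) = 10.36.
- For improvement, the standardised effect is 10/37 = 0.270. The expected z is 0.270 × 10.36 = 2.80, and power is Φ(2.80 − 1.96) ≈ 80%.
- For the final score without baseline, take a baseline SD of 75 and r = 0. The SD of the final score is about √(75² + 37²) = 83.6, ignoring truncation. The expected z is (10/83.6) × 10.36 = 1.24, and power is Φ(1.24 − 1.96) ≈ 24%.

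So ignoring baseline takes power to about a quarter before any banding. Banding and the 3-df test lower it further.

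**Step 3: simulation.** Each setting used 2,000 simulated trials (Monte Carlo standard error about 1 percentage point). Final score = baseline − improvement, limited to 0–500 and cut into the four bands. Power at two-sided 0.05:

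| Setting | Pearson, 3 df | Proportional odds, no baseline | Proportional odds + baseline | t-test on improvement |
|---|---|---|---|---|
| 322 + 161, r = 0 | 12–24% | 17–30% | 53–56% | 79–81% |
| 400 + 200, r = 0 | 12–30% | 21–38% | 61–64% | 86–89% |
| 322 + 161, r = 0.4 | 17–21% | 25–32% | 61–62% | 80–81% |
| 322 + 161, r = 0.7 | 23–34% | 33–45% | 75–76% | 81% |

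The rows with r = 0 span six baselines (mean 200–300, SD 50–90). The other two rows span three (mean 230–275, SD 70–80). In the first row, Pearson's 24% comes from the lowest and narrowest baseline (mean 200, SD 50); the other five give 12–16%. With no true effect, every test rejected in about 5% of trials.

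**Step 4: if the variable has two classes.** Order then plays no part. For a drop of at least 50 points (an assumed cut) at 322 + 161 with r = 0, chi-squared has about 27–31% power. For a final score below 175 (also an assumed cut), chi-squared has about 16–20%, and logistic regression adjusted for baseline about 29–35%.

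**The case against.** The strongest objection is that the document plans no test of the bands. They appear in the description of the instrument. The chi-squared sentence closes a generic list of tests by data type, and it could refer to grouped covariates such as age or disease duration, or to a two-class responder. An article may also leave the choice of variable to the full protocol or analysis plan. This stands, and it is why the point is conditional. The omission is not the finding. What the article does fix is the test, and that test suits the likeliest variable badly.

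Chi-squared is also a valid test, holding its 5% error rate, and the frequencies and percentages reported beside it would show direction. Both are true. The adjusted ordinal analysis would itself miss the planned effect in almost half of trials at 53–56% power, so discordance with the continuous result would become less likely but would not disappear.

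A reader might infer three stronger things that the documents do not support:
- That the trial is underpowered. It is sized on mean improvement, and that comparison keeps about 80%.
- That the loss comes mainly from ignoring order. In the first row of the table, order alone moves power only from 12–24% to 17–30%; baseline adjustment brings the rest.
- That a narrow pair of figures, such as 12–16% against 53–56%, can be attached to this trial. Such figures need a baseline distribution and a correlation that the document does not give.

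**Conclusion.** The point holds conditionally. If the transformed categorical variable is the four IBS-SSS bands, Pearson's chi-squared is a poor choice: power is roughly 12–34% for the plan's own effect, against roughly 53–76% for an ordinal analysis adjusted for baseline score. The exact figures depend on assumed baseline means, SDs and correlations and on whether 483 or 600 patients are analysed, but the adjusted analysis was clearly better in every setting tried. If the variable is a two-class final state, the argument from order falls away and a smaller loss from ignoring baseline remains. The effect is confined to a supporting analysis. The overlap at 175 is a genuine slip in the text, but touches only patients who score exactly 175.

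**What to change.** Name the categorical variable, its cut points and its time point. Then:
- If it is the severity bands, state which band a score of 175 belongs to. Compare arms with a proportional-odds model with terms for arm, baseline IBS-SSS and IBS subtype (the stratification factor). Report a common odds ratio with 95% confidence interval and check proportionality. If proportionality fails, a linear trend on band scores adjusted for baseline is a workable fallback.
- If it is a two-class final state, use logistic regression with the same covariates.
- Keep Pearson's chi-squared for unordered categories only, and keep the continuous score as the primary comparison.

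The cost is a few sentences, a standard SPSS procedure, one model assumption to check and slightly more analysis work. No new data are needed.
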